### Five-year follow-up

All participants will be asked to consent to a telephone call to complete the WOMAC, SF-12 and MAPT annually until five years after TKR. In addition, data linkage with the Australian National Joint Replacement Registry will be used to verify incident primary or revision hip or knee replacement surgeries occurring in our cohort during this five year period.

### Sample size

Based on preliminary data [35], a sample size of 600 participants will be required. This sample size will provide 80% power of detecting a 15% difference in the proportion of treatment responders (OMERACT-OARSI responder criteria [45]) between the groups, and allows for up to 10% cross-over of treatment allocation and a 15% loss to follow-up [61]. In addition, this sample size will provide more than 90% power to detect clinically significant differences in each of the continuous secondary outcome measures.

### Statistical analysis

Statistical analysis will be by intention to treat and coded to ensure blinding to treatment allocation. For continuous data, two-way repeated measures ANOVA incorporating treatment groups at the three follow-up time points (6 weeks, 6 months and 12 months) will be carried out. The significance of any differences in dichotomous data (OMERACT-OARSI treatment responders, proportion of patients reporting sufficient leisure time physical activity, number of adverse events) will be tested using generalised estimating equations or linear mixed model. If there are chance imbalances in baseline patient characteristics hypothesised to influence the main outcomes, then statistical techniques that allow adjustment for confounding variables will be used as secondary analyses. If there are more than 5% missing data, sensitivity analysis allowing for different assumptions such as the best or worst possible scenario will also be reported for the main outcomes of the study.

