## Methods

The MARKER (Maximum Recovery after Knee Replacement) Study is a multicentre randomised controlled trial that will be conducted in 10 large public and private hospitals in Australia. Participants will be required to provide written informed consent prior to starting the study. Ethics approval has been obtained from the University of Sydney Human Research Ethics Committee and from the Ethics Review Committee (RPAH Zone) of the Sydney South West Area Health Service using the National Ethics Application Form . The MARKER Study has been registered at the Australian and New Zealand Clinical Trials Registry (ACTRN12609000054213).

Potential participants will be screened and recruited at the orthopaedic pre-admission clinic. Inclusion criteria are: (i) aged between 45 to 74 years, (ii) planned unilateral or bilateral primary TKR, and (iii) able to be discharged home from the orthopaedic ward. Exclusion criteria include: (i) previous unicompartmental replacement or tibial osteotomy on the same knee, (ii) previous lower limb joint replacement surgery within the last six months, (iii) further lower limb joint replacement surgery anticipated within the next 12 months, (iv) major co-morbidity precluding aerobic exercise at 50–60% maximum heart rate, (v) rheumatoid arthritis, (vi) major neurological conditions, or (vii) inability to return to one of the participating sites for outpatient exercise classes.

There will be no change to usual medical or rehabilitative care during the peri-operative inpatient period. After TKR, but before discharge from the orthopaedic ward, participants will be randomly allocated to either the novel rehabilitation strategy or usual rehabilitative care specific for the orthopaedic centre or surgeon (control group). The randomisation schedule will be generated a priori using a computer generated random number sequence by an independent researcher with no participant contact, in varying blocks of four or six, and stratified by recruitment site and by unilateral or bilateral TKR. Allocations will be sealed in opaque and consecutively numbered envelopes with a clear audit trail.

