### Outcomes assessments

Assessments will be conducted at baseline (pre-admission clinic), and 6 weeks, 6 months and 12 months after randomisation by assessors blinded to treatment allocation. Demographic information collected at baseline will include height, weight, socioeconomic data (highest level of education completed, health insurance status, employment status, occupation), history of lower limb arthritis and joint surgery and the 19-item Hospital for Special Surgery Knee Replacement Expectations Survey [37,38]. This survey has been tested for internal consistency (Cronbach's alpha = 0.77) and test-retest reliability [37].

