#### Primary outcomes

The primary outcomes will be self-reported knee pain and physical function measured on the Western Ontario and McMaster Universities (WOMAC) Osteoarthritis Index, using a 5-point Likert scale (WOMAC LK3.1) [39]. The WOMAC consists of 24 items covering three subscales: pain (five items), stiffness (two items) and physical function (17 items). The pain and physical function subscale will be used, each subscale transformed to a score ranging from 0 (no pain or difficulty) to 100 (maximum pain or difficulty). The WOMAC is a widely-used questionnaire specifically designed to evaluate knee and hip OA [40,41]. Its clinimetric properties have also been validated in patients undergoing TKR [42-44].

Responses on the WOMAC will also be dichotomised according to the OMERACT-OARSI responder criteria for OA [45], i.e. treatment responders are defined as those participants achieving ≥20% improvement in both pain and physical function scores and an absolute change of ≥10, or ≥50% improvement in pain or physical function scores and an absolute change of ≥20 on the WOMAC.

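### The primary WOMAC analysis omits the baseline score and the randomisation strata and adjusts only secondarily, after a chance imbalance: precision is lost, but the estimate is not biased

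*Protocol article*

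**What the plan says.** The protocol article names two primary outcomes (Primary outcomes): "The primary outcomes will be self-reported knee pain and physical function measured on the Western Ontario and McMaster Universities (WOMAC) Osteoarthritis Index". Both are scored 0 to 100. The section Outcomes assessments shows that they are measured before surgery as well as afterwards: "Assessments will be conducted at baseline (pre-admission clinic), and 6 weeks, 6 months and 12 months after randomisation by assessors blinded to treatment allocation".

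The model for continuous data is given under Statistical analysis: "two-way repeated measures ANOVA incorporating treatment groups at the three follow-up time points". Baseline is neither one of the visits nor a covariate. Randomisation is "stratified by recruitment site and by unilateral or bilateral TKR" (Methods), and these factors do not appear in the model either.

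The rule on covariates is "If there are chance imbalances in baseline patient characteristics hypothesised to influence the main outcomes, then statistical techniques that allow adjustment for confounding variables". The same sentence fixes its status: "adjustment for confounding variables will be used as secondary analyses".

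Dichotomous outcomes "will be tested using generalised estimating equations or linear mixed model". The article puts three outcomes under that label: OMERACT-OARSI responders, sufficient leisure-time activity, and a tally of adverse events.

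**The concern.** A pre-operative WOMAC score would normally be expected to predict the post-operative score. Leaving it out of the primary model puts explainable variation into the error term. The adjustment rule does not recover this, because it operates only in a secondary analysis and only when an imbalance happens to appear. Whether to adjust, and for what, then depends on the observed arms. The better basis is prognostic value judged beforehand.

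Stratified randomisation balances the arms on site and on unilateral or bilateral surgery. An analysis that ignores those factors uses a standard error that does not reflect that balance.

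Two smaller matters concern the binary outcomes. A linear mixed model in its usual form assumes one residual variance, whereas the variance of a binary outcome is p(1 − p) and changes as patients recover. A number of events is also not a dichotomous variable.

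At stake are the power of the main comparison, the width of its confidence interval, and freedom of choice in the adjusted analyses.

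**Working it through.** **The plan's own figure.** Sample size gives 600 participants for 80% power to detect a 15% difference in responders, allowing 10% cross-over and 15% loss. Alpha and the control rate are not stated, so 600 cannot be confirmed, but it is attainable. Assuming 55% against 70% and two-sided 0.05, 163 per arm are needed, and 163 / (1 − 0.2)² / 0.85 ≈ 300 per arm, or 600. That 80% belongs to a binary outcome. No power is stated for continuous WOMAC. The claim of more than 90% concerns the continuous secondary outcomes.

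**Baseline score.** Participants assessed: 600 × 0.85 / 2 = 255 per arm. The baseline to follow-up correlation r is not given, so 0.3 to 0.5 is assumed. Adjusting for baseline multiplies single-visit residual variance by 1 − r². For an effect with unadjusted power P, adjusted power is Φ[(1.96 + z_P) / √(1 − r²) − 1.96], where 1.96 + z_P is 2.80 for P = 80% (an effect of 0.248 SD at 255 per arm) and 3.24 for P = 90% (0.287 SD).

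| r | 1 − r² | Variance reduction | Power, from 80% | Power, from 90% |
|---|---|---|---|---|
| 0.3 | 0.91 | 9% | 83.6% | 92.5% |
| 0.4 | 0.84 | 16% | 86.4% | 94.3% |
| 0.5 | 0.75 | 25% | 89.9% | 96.3% |

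These figures are for a contrast at one visit. If all four occasions are equally correlated (also assumed), the reduction for the effect averaged over three follow-ups is 3r² / (1 + 2r): 0.27/1.6 = 17%, 0.48/1.8 = 27% and 0.75/2 = 38%.

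**Strata.** Let s be the share of variance between strata, assumed to be 1% to 10%. Ignoring strata overstates the standard error by 1/√(1 − s). True two-sided alpha is 2[1 − Φ(1.96/√(1 − s))].

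| s | SE ratio | True alpha | Power without strata | Power with strata |
|---|---|---|---|---|
| 0.01 | 1.005 | 0.049 | 80.1% | 80.4% |
| 0.05 | 1.026 | 0.044 | 80.6% | 82.0% |
| 0.10 | 1.054 | 0.039 | 81.3% | 84.0% |

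**Linear model for binary data.** Assume responder rates of 60%, 75% and 90% at the three visits, 255 per arm. Then p(1 − p) is 0.24, 0.1875 and 0.09, with mean 0.1725. The linear model uses one standard error, √(2 × 0.1725/255) = 0.0368, and fitting such a model to simulated data gave the same value. The true standard errors are √(2 × 0.24/255) = 0.0434, then 0.0383 and 0.0266. The ratios are 0.85, 0.96 and 1.38, and the actual alpha is about 0.097, 0.060 and 0.007. With rates of 70%, 75% and 80% the error is only −6% to +8%. For the effect averaged over visits with a constant rate, simulated type I error was 0.046 to 0.056, close to nominal.

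**The case against.** An unadjusted comparison is valid under randomisation, and the primary test does not depend on any observed imbalance. A reader might infer from the adjustment rule that the main result is biased, or that its type I error is inflated by picking covariates. The text does not support either. Adjustment is secondary, candidates are limited to characteristics thought beforehand to affect the outcome, and the analysis is coded. Coding hides which arm is which but not the size of an imbalance, so freedom of choice remains, though only in the secondary analyses.

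A reader might also infer that the trial's stated 80% power would rise to 90%, or that the omission wastes a countable share of the 600 participants. It cannot be put that way. The 80% refers to responders, whose definition already uses improvement from baseline, and the correlation is assumed. The gains illustrate continuous WOMAC only.

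Nor do the omitted strata point to false positives: the error makes the test slightly conservative. Silence on strata in a one-paragraph summary is also weak evidence of exclusion, since a full plan may well include them. The baseline point is firmer. The article names the model and its visits and confines adjustment to a conditional secondary analysis, and a plan that followed this would keep the defect.

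On binary outcomes, GEE is named first, the word linear may be loose for generalised, and link functions are commonly left to the analysis plan. That largely stands, so this part is minor. Likewise, the adverse event entry may be a loose label for participants with an event.

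**Conclusion.** The point holds as one of efficiency and pre-specification. The primary continuous analysis forgoes information already collected, and the imbalance trigger gives the primary test nothing in return. The loss is about 4 to 10 power points for an effect with 80% unadjusted power, or about 2.5 to 6 for one with 90%. It rests on an assumed correlation of 0.3 to 0.5 and a single-visit contrast. The effect of the strata is small and conservative under the assumed 1% to 10% share of variance.

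The linear model for binary data is a lesser matter. It misstates standard errors materially only for visit-specific contrasts when responder rates differ widely between visits. The documents give no such rates, so they do not support concluding that the responder analysis is invalid. Listing a count as dichotomous is a plain slip that wording can settle.

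**What to change.** For WOMAC pain and function, make the primary analysis a linear mixed model with treatment, visit, treatment × visit, baseline score, site and unilateral or bilateral TKR, all specified in advance and included whatever the observed balance. Delete the imbalance trigger.

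For binary outcomes, remove the linear mixed model option. Specify GEE with a binomial variance, and report the difference in proportions, which is the quantity the sample size is built on. An adjusted odds ratio would be a different quantity.

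For adverse events, define the dichotomous outcome as participants with at least one event.

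The cost is mainly wording, since the baseline score and strata are already collected. There is one small downside. Ten sites crossed with unilateral or bilateral surgery make 20 strata, and some bilateral ones may hold few participants. The plan should say in advance how sparse strata will be pooled if a binary model needs it.

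### Repeated measures ANOVA for the two primary WOMAC scores drops anyone who misses a visit, so intention to treat is only partly realised; use a mixed model

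*Protocol article*

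**What the plan says.** All references are to the protocol article.

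- Primary outcomes: "The primary outcomes will be self-reported knee pain and physical function", from the WOMAC, each subscale rescaled to 0-100. These are continuous scores.
- Statistical analysis, principle: "Statistical analysis will be by intention to treat".
- Statistical analysis, continuous data: "two-way repeated measures ANOVA incorporating treatment groups at the three follow-up time points", namely 6 weeks, 6 months and 12 months.
- Statistical analysis, dichotomous data, including OMERACT-OARSI responders: generalised estimating equations or a linear mixed model.
- Statistical analysis, missing data: "If there are more than 5% missing data, sensitivity analysis allowing for different assumptions such as the best or worst possible scenario" will be reported as well, for the main outcomes. The article states no handling of missed visits in the main analysis.
- Sample size: the total of 600 "allows for up to 10% cross-over of treatment allocation and a 15% loss to follow-up".

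**The concern.** Classical two-way repeated measures ANOVA needs a value in every visit cell for each participant. One missed visit removes the whole participant, including the scores that were obtained. The plan names methods that keep partly observed participants, but only for dichotomous data. It is therefore hard to read the ANOVA as shorthand for a mixed model.

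At stake is the primary comparison. It would rest on participants who completed every visit and not on all those randomised. Completers can differ from the rest, and the difference can depend on arm: participants are not blinded, and only the novel arm is asked to attend classes twice a week for eight weeks. Information is also lost without need.

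The second question is whether the one sensitivity scenario named would tell the reader much at the loss the trial allows for.

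**Working it through.** **Inputs.** From Sample size: 600 participants, 80% power, 15% difference in responders, 10% cross-over, 15% loss. From Statistical analysis: three follow-up visits and a 5% trigger. Assumed because not stated: 1:1 allocation (300 per arm), two-sided 5% level, the 15% difference read as percentage points, equal loss in both arms, and control responder rates scanned from 30% to 80%.

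**1. The plan's own figure.** Cross-over of 10% in both arms dilutes the effect to 15 x (1 - 0.10 - 0.10) = 12 points. With control 30% and novel 45%, the diluted rates are 31.5% and 43.5%, with mean 37.5%. Per arm,

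n = [1.96 x sqrt(2 x 0.375 x 0.625) + 0.842 x sqrt(0.315 x 0.685 + 0.435 x 0.565)]^2 / 0.12^2, about 254.3, so 255.

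Dividing by 0.85 gives 300 per arm, or 600 in total. The stated size is attainable. It cannot be confirmed, because other control rates give other totals (638 at 40%, 626 at 50%, 560 at 60%). Nothing below depends on it.

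**2. Participants dropped by the ANOVA (WOMAC scores).**

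- All loss is dropout by 12 months: 0.15 x 600 = 90 excluded, 510 kept.
- In addition 5% miss each of the two earlier visits independently (assumption): 0.85 x 0.95^2 = 0.767 complete, so about 460 kept and about 140 excluded.
- 5%, 10% or 15% miss each of the three visits independently (assumption): 0.95^3 = 85.7%, 0.90^3 = 72.9% or 0.85^3 = 61.4% complete.

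**3. Best and worst case (responder outcome, a separate analysis).** Let L be the proportion missing in each arm and 15 points the difference among those observed. With opposite extremes in the two arms,

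worst = (1 - L) x 15 - 100L; best = (1 - L) x 15 + 100L.

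| L | Worst (points) | z, worst | Best (points) |
|---|---|---|---|
| 5% | 14.25 - 5 = +9.25 | 2.3 to 3.2 | +19.25 |
| 10% | 13.5 - 10 = +3.5 | 0.9 to 1.2 | +23.5 |
| 15% | 12.75 - 15 = -2.25 | -0.55 to -0.72 | +27.75 |

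The z values are pooled tests with 300 per arm over the control rates scanned. The differences themselves do not depend on the control rate. The worst case reaches zero at L = 0.15/1.15 = 13.0%, and it loses significance at about 6% to 8% missing.

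**4. The other reading of the scenario.** If all missing participants in both arms are set to respond, or all to not respond, the difference at L = 15% is 0.85 x 15 = +12.75 points, with z about 3.1 to 5.1. It stays significant.

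**The case against.** Five objections deserve an answer.

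- **The two parts concern different outcomes.** This stands. The 15-point effect is on responders, whose planned methods keep participants with some visits missing. The -2.25 to +27.75 range says nothing about the ANOVA, and no figure for bias in the WOMAC comparison can be derived from the document.
- **Intention to treat may mean only analysis by allocated arm,** which matters given the 10% cross-over. On that reading the ANOVA does not contradict it. A reader might infer an outright contradiction, but the text supports only an incomplete realisation: allocation is respected, yet some randomised participants are left out.
- **The sensitivity wording is open.** The scenario is introduced as an example among different assumptions, and an analysis plan that is not shown may add others. This stands, so the second part is a suggestion to add, not a charge of omission. It does not touch the ANOVA, which is a stated method.
- **The scenario can be informative.** A reader might infer that it reverses any plausible finding. It does not: the planned effect survives with significance at 5% missing and stays positive at 10%. At 15% missing, any observed difference above 15/0.85 = 17.6 points stays positive. A result that survives such bounds is robust.
- **The 15% is an allowance, not a forecast,** and the 5% intermittent missingness is assumed. Both are correct, and the counts are conditional on them.

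**Conclusion.** The main point holds. Read literally, the plan gives both primary WOMAC scores a complete-case method beside an intention-to-treat statement. At the allowed 15% loss this excludes at least 90 of 600, and about 140 under the assumption of 5% missing at each earlier visit. The size and direction of any resulting bias are unknown.

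The secondary point holds in a limited form. At 15% missing, the result for the planned responder effect depends on how an undefined scenario is read: -2.25 to +27.75 points with opposite extremes, +12.75 with the same value in both arms. A reader might infer that the trial's result would be overturned into harm. It would not: -2.25 is far from significant, so the worst case means loss of significance with a small change of sign. These figures rest on equal loss by arm, 1:1 allocation and 15% read as percentage points; the significance statements also assume a two-sided 5% level.

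**What to change.** For WOMAC pain and function, replace the repeated measures ANOVA with a likelihood-based linear mixed model containing treatment, visit and treatment-by-visit. Include every randomised participant with at least one follow-up score. This is valid if scores are missing at random. It recovers the scores of those who missed some visits. Participants with no follow-up score still contribute none, and the document does not show how many of the 90 they would be.

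For the sensitivity analysis, say what the best and worst case assign to missing participants in each arm. Add beside it a graded delta analysis: shift the imputed outcomes in stepped amounts and report the point at which the conclusion changes.

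The cost is a little more analysis work. No new data, visits or participants are needed.

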### Health economic analysis

The economic evaluation will consist of a trial-based cost-utility analysis to assess the incremental cost per quality-of life-year (QALY) of the novel rehabilitation strategy compared to usual care. The primary analysis will be conducted from the perspective of the health sector. A secondary analysis will entail a societal perspective in which the additional costs (and cost savings) associated with use of community services, absenteeism and presenteeism will be factored in.

In the primary analysis, costs of healthcare services will be valued at standard rates published by the Australian Government: the Medical Benefits Scheme standard fees for medical services and procedures, the Pharmaceutical Benefits Scheme cost for medications and the Australian Refined Diagnosis Related Groups (AR-DRG) cost weights for hospital services. These will be factored with levels of utilisation to estimate the costs of healthcare use in participants.

In the secondary analysis, costs of community services will be based on the self-reported costs of participants. The costs of presenteeism will be estimated by the number of days worked weighted by the rate of presenteeism multiplied by the average wage rate for the relevant employment category. The costs of absenteeism will be estimated by the number of days absent from work multiplied by the average wage rate for the relevant employment category. For those engaged in unpaid work, the national average wage rate will be used. A separate set of cost-utility ratios will be presented in this secondary analysis incorporating the wider costs (and cost savings) to the community.

Health state utilities required to estimate QALY will be based on measures obtained from the SF-12 and transformed into health state utilities via the SF-6D algorithm [62]. Although no survival difference is expected between the two groups at 12 months, average quality of life over 12 months for each participant will be estimated and weighted by survival up to 12 months to determine, for each patient, a measure of QALY after TKR. Given likely variations in the 'usual care' across sites, separate incremental cost-utility ratios will be estimated for broad categories of usual care (inpatient or outpatient). Sensitivity analysis will test uncertainty in key parameters such as the selection of cost weights and statistical variation in quality of life scores.

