### Health economic outcomes

Participants will prospectively record in a patient diary the following:

• presenteeism (self-reported capacity to work or perform daily activities) [58-60]

• instances of absenteeism

• use of healthcare and community services

• out-of-pocket costs of community services

These data will be collected over three six-week time periods from: (i) discharge from acute care, (ii) the 6-week follow-up assessment, and (iii) the 6-month (26-week) follow-up assessment.

Presenteeism will be rated from 0% (unable to do usual work/activities) to 100% (fully functioning). Absenteeism is defined as days off work (including home, volunteer or carer duties) due to TKR. The use of healthcare (e.g. visits to medical practitioners, physiotherapists, hospitalisation) and community (e.g. meals on wheels) services will be recorded in terms of the type of service, date of use and number of hours/days. Costs of community services will be the out of pocket costs incurred by participants. The use of medication will be included as a health economic outcome and will be collected at the time of each follow-up assessment.

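### In the secondary societal analysis, the presenteeism cost as written values work done rather than work lost, so a higher capacity score raises the charge

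*Protocol article*

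**What the plan says.** Health economic outcomes introduces the diary item as "presenteeism (self-reported capacity to work or perform daily activities") and gives its scale: "Presenteeism will be rated from 0% (unable to do usual work/activities) to 100% (fully functioning"). A higher score is therefore a better result. This is the only presenteeism scale in the article.

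Health economic analysis turns the score into money. The presenteeism cost is "estimated by the number of days worked weighted by the rate of presenteeism multiplied by the average wage rate", with wages taken by type of employment. The next sentence treats absence as a loss: "The costs of absenteeism will be estimated by the number of days absent from work multiplied by the average wage rate".

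Both items enter one place only: "A secondary analysis will entail a societal perspective in which the additional costs (and cost savings) associated with use of community services, absenteeism and presenteeism" are counted. The main economic analysis does not use them: "The primary analysis will be conducted from the perspective of the health sector".

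**The concern.** The scale and the cost formula do not fit together. A productivity cost should be zero for someone who is at work and fully functioning, and should grow as capacity falls. The stated product does the opposite, and it stands beside an absenteeism cost that does measure a loss. The two productivity items in the societal total therefore run in opposite directions.

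The article promises a separate set of cost-utility ratios from the societal perspective, and its Discussion anticipates savings to the wider community. If the novel strategy improves work capacity, which the trial hopes to show, the formula taken literally charges that arm for the improvement.

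**Working it through.** The article gives no presenteeism cost, so there is no figure to reproduce. The check evaluates the formula as written against a lost-productivity form.

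**Inputs**
- P: presenteeism score as a proportion, 0 = unable, 1 = fully functioning (Health economic outcomes).
- A: days absent. D: working days in the period, so days worked = D − A.
- w: daily wage, set to 1, so results are in daily wages.
- D = 30 is an assumption: one six-week diary window ("These data will be collected over three six-week time periods") at 5 working days a week. The article gives no values for A, P or w, so those below are illustrative.

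**Formulas**
- Presenteeism as written: (D − A) × P × w
- Presenteeism as lost productivity: (D − A) × (1 − P) × w
- Absenteeism (same in both): A × w

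**Step 1. Extremes, D = 30, A = 0**
- P = 1: as written 30 × 1 = 30; as a loss 30 × 0 = 0.
- P = 0 while at work: as written 30 × 0 = 0; as a loss 30 × 1 = 30.
- A person absent for all 30 days has an absenteeism cost of 30 and no presenteeism cost. As written, the fully functioning worker is charged the same 30.

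**Step 2. Direction of the presenteeism component**

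The derivative of (D − A) × P × w in P is (D − A) × w, which is positive whenever any days are worked. A higher score always raises the charge.

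**Step 3. Size for a 10-point difference in score, equal days worked in both arms**

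As written, the better arm is charged 0.1 more per day worked; as a loss it is charged 0.1 less. The error in the between-arm difference is 0.1 + 0.1 = 0.2 daily wage per day worked:

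| Days worked (assumed) | Error, daily wages |
|---|---|
| 45 | 0.2 × 45 = 9 |
| 60 | 0.2 × 60 = 12 |
| 90 | 0.2 × 90 = 18 |

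Ninety days is all three windows (3 × 30) with no absence at all. It is an upper end, because the first window starts at discharge from acute care.

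**Step 4. Absenteeism plus presenteeism, D = 30**

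| Arm | As written: A + (D − A)P | Corrected: A + (D − A)(1 − P) |
|---|---|---|
| P 0.9, A 5 | 5 + 22.5 = 27.5 | 5 + 2.5 = 7.5 |
| P 0.6, A 10 | 10 + 12 = 22 | 10 + 8 = 18 |
| Difference (better − worse) | +5.5 | −10.5 |

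| Arm | As written | Corrected |
|---|---|---|
| P 0.6, A 10 | 10 + 12 = 22 | 10 + 8 = 18 |
| P 0.5, A 20 | 20 + 5 = 25 | 20 + 5 = 25 |
| Difference (better − worse) | −3 | −7 |

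In the first pair the sign reverses. In the second it is right, but the saving is too small.

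**The case against.** **The authors may have meant the rate as the share of productivity lost.** The formula would then be correct and only a term would be undefined. The sources cited for presenteeism are not at hand, and this is a condensed article. But the article defines the score once, as capacity retained, and nowhere reverses it or takes its complement. The intention may have been sound; the rule as written is not.

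**The product might be entered as a saving**, since the article speaks of costs and cost savings. The article calls the product a cost, and the reading fails in any case. The true loss is A + (D − A)(1 − P) = D − (D − A)P, so crediting (D − A)P already allows for days absent. Adding the separate absenteeism cost would count absence twice. In the first pair of Step 4 the credit alone gives −22.5 − (−12) = −10.5, the right answer; adding the absenteeism difference of 5 − 10 = −5 makes it −15.5.

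**The reach is limited.** This objection stands. A reader might infer that the whole productivity component is reversed, or that better recovery always raises an arm's societal cost. The documents do not support either. The absenteeism cost has the right sign. With w = 1 the combined total as written is A + (D − A)P, whose derivative in A is 1 − P, never negative. At a fixed score, fewer days absent therefore never raise the total, and the second pair in Step 4 shows a better arm that remains cheaper.

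**The score is collected in usable form.** This also stands. The diary record supports either weighting, so recruitment and data collection are not affected.

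**Conclusion.** The point holds for the presenteeism part of the secondary societal analysis. On the article's own scale, the stated formula prices work done and calls it a cost. That component always moves the wrong way with the score, by 0.2 daily wage per day worked for each 10-point difference between arms with equal days worked.

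The effect on the combined productivity cost depends on whether the gain is in capacity or in days absent. The illustrations range from a reversed sign (+5.5 against −10.5 daily wages) to a saving understated by 4 (−3 against −7). They rest on an assumed 30 working days and on chosen values of A and P; the direction of the presenteeism error rests on none of these.

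It would go too far to say that the trial's economic conclusion is reversed. The primary health-sector analysis contains no presenteeism cost, and the clinical outcomes and sample size do not use the formula. Whether a societal ratio would change direction also depends on the other costs and on the QALY difference, for which the article gives no figures.

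**What to change.** In Health economic analysis, replace the presenteeism sentence with this rule: presenteeism cost = days worked × (1 − presenteeism rate/100) × average wage rate for the relevant employment category, where the rate is the diary score defined under Health economic outcomes. Keep absenteeism as days absent × wage rate. The two items then cover separate days and add without overlap.

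The cost is one line of wording and no new data. Make the change before the economic analysis is run, so that the formula is not altered after the results are known.
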